|                      | 
 
Costs per child and sample collection (based on direct costs).
 
 
Secondary exploratory endpoints in the event of SARS-CoV-2 cases being detected
 
 
Proportion of positive PCR tests
 
Proportion of positive serological tests, correlation between positive PCR and seroconversion between first and second serological test
 
Number and cost of swabs (throat and nose) / saliva samples per detected case of SARS-CoV-2 infection
 
                                                                                                                                                                                                                                                                                                                                                                                                                                                                                                                                                                                                                                                                                                                                                                                                                                                                                                                                                                                                                                                                                                                                             |

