#### 4.3.1.5 Additional offers for symptom-based testing of symptomatic children and childcare workers in modules 1-3

According to the regulations in force at present, children with infection symptoms are not allowed to attend daycare centers and symptomatic childcare workers are obliged to stay off work. This restriction will concern all study participants, irrespective of which study module the children and childcare workers are enrolled in.

According to the study protocol for module 4, symptomatic children, symptomatic childcare workers and symptomatic household members of participating children and childcare workers will be tested for SARS-CoV-2.

In modules 1-3, symptomatic children and/or childcare workers and their symptomatic household members will be offered the option to arrange an appointment for a oropharyngeal swab for SARS-CoV-2 in the COVID-19 testing centre at the University Hospital Würzburg, building D20.

Parents/guardians of children participating in modules 1-3 will be given the option to perform sample collection (mid-turbinate swabs, saliva samples) of their symptomatic children themselves.

If they do not take up either of these offers, they will be asked to notify the central study office of the result of the SARS-CoV-2 test performed by third parties (e.g. general practitioner).

All symptomatic persons (in the case of symptomatic children the parents/guardians) will be asked to provide information on the time of disease onset and the observed symptoms in a standardised questionnaire.

Medical care for symptomatic persons will not be provided within this study, but will lie in the responsibility of the participants' primary care physicians/pediatricians.

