#### 4.3.1.8 Case Module

In the event that a child, household member or childcare worker is tested positive for SARS-CoV-2, the diagnostic laboratory will notify the local health authorities in accordance with §7 Infection Protection Act ("Infektionsschutzgesetz"). Persons tested positive for SARS-CoV-2 will be obliged to follow the instructions of the local health authorities.

The local health authorities will be responsible for deciding whether or not the daycare centre attended by the SARS-CoV-2 positive child / where the SARS-CoV-2 positive childcare worker works can remain open.

Re-admittance to the daycare centre will be subject to the instructions issued by the local health authorities.

Household members of participants tested positive for SARS-CoV-2 will be tested according to the instructions of the local health authorities. Serology for SARS-Cov-2 antibodies will be carried out 2 weeks after the end of the quarantine period imposed by the local health authorities if written informed consent was obtained for venous blood sampling within the study.

Unless the local health authorities issue instructions to the contrary, the daycare unit (the entire daycare centre or the relevant group) of the SARS-CoV-2 positive child/childcare worker will be tested for SARS-CoV-2 twice a week for a duration of 2 weeks after the date of diagnosis.

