#### **Exploratory Analyses regarding effectiveness of the intervention**

- Proportion of all mid-turbinate swabs tested positive for SARS-CoV-2 (PCR)
- Proportion of all saliva samples tested positive for SARS-CoV-2 (PCR)
- Proportion of parents/siblings/others among all persons tested for SARS-CoV-2 (PCR) [Module 4]
- Proportion of absent days due to respiratory symptoms
- Proportion of absent days due to SARS-CoV2 infection of child and/or SARS-Cov-2 infection of a family member/other contact person (quarantine)
- Closures of daycare groups / daycare centers by the health authorities due to positive SARS-CoV-2 results within the research study
- Closures of daycare groups / daycare centers by the health authorities due to other causes
- Proportion of children and childcare workers with positive serological test result (antibodies) before and after the observation period of 12 weeks

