## **7.2 Data analysis methods**

The primary endpoints will be estimated as 95% confidence intervals using the Wilson score method. Due to the purely exploratory nature of all analyses and the fact that the four modules will be implemented in separate daycare centers, the significance level will not be adjusted for multiple testing and all analysis results will be interpreted with the necessary caution. The significance level will be set to 5% for all analyses. In a first step, descriptive analyses

(frequency (percent), mean (SD) or median (IQR)) will be reported for all endpoints. The analysis of the secondary endpoints drop out rate, initial rate of consent, acceptance of blood sampling (stratified by childcare workers and parents), proportion of positive serological tests and proportion of positive PCR tests will, in a first step, compare all four groups using test procedures such as the Chi-squared-test, ANOVA or the Kruskal Wallis test as appropriate. Subsequently, pairwise comparisons will be carried out using appropriate post-hoc tests. The rate of acceptance will first be compared between all modules 1 to 3 using the chi-squared test. Analysis of the development of the psychosocial factors over time will be stratified by monitoring module and will use tests for repeated measurements such as the McNemar test, Repeated Measurements ANOVA and the Friedman test. In addition, baseline values and the follow-up values after 12 weeks will be compared between modules using appropriate tests such as the chi-squared test and ANOVA or non-parametric tests followed by post-hoc tests. Potential predictors of the rate of acceptance will be analysed (overall for all modules combined and stratified by module) in univariable analyses using the chi-squared test and, if a sufficient sample size is obtained, additionally using multivariable logistic regression. The analysis of costs, the proportion of absent days and data on the closure of daycare groups will be restricted to descriptive methods. The development of seroprevalence data over time will be reported using descriptive methods, possibly including graphical displays. The results of the children interviews will be reported descriptively using frequencies. If possible, an ICC value (intraclass correlation) for the daycare centers will be calculated as a basis for sample size estimation for a future cluster randomised study. All analyses will be performed in SAS, R or SPSS.

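### PCR positivity is tested across all four modules at 5%, although Modules 1–3 screen asymptomatic people and Module 4 tests only symptomatic people, so the contrast differs by design

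*Protocol*

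**What the plan says.** The Synopsis (section 1.4) lists "Proportion of positive PCR tests" among the secondary exploratory endpoints that apply if cases are found. Section 7.2 places it in a list of endpoints to be compared between modules: "proportion of positive serological tests and proportion of positive PCR tests will, in a first step, compare all four groups". The choice of method is left open, "using test procedures such as the Chi-squared-test, ANOVA or the Kruskal Wallis test as appropriate", and pairwise post-hoc comparisons come after that. On the error rate the section states: "The significance level will be set to 5% for all analyses".

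Section 7.1, under the exploratory effectiveness analyses, fixes the unit as the sample: "Proportion of all mid-turbinate swabs tested positive for SARS-CoV-2 (PCR", with a matching item for saliva samples. The same list counts serology per child or worker. The only PCR item it marks for Module 4 is "Proportion of parents/siblings/others among all persons tested for SARS-CoV-2 (PCR) [Module 4", which describes who was tested rather than how many were positive.

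Sections 1.7 and 4.3.1 set out who is tested:
- Modules 1 and 3 sample asymptomatic children and workers twice a week, and Module 2 samples them once a week, for 12 weeks.
- Module 4 tests children, workers and household members only when they have symptoms.

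Two further streams exist. In Modules 1–3, under section 4.3.1.5, parents "will be given the option to perform sample collection (mid-turbinate swabs, saliva samples) of their symptomatic children themselves". After a case, under section 4.3.1.8, the daycare unit "will be tested for SARS-CoV-2 twice a week for a duration of 2 weeks after the date of diagnosis".

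**The concern.** A share of positive samples depends on how many samples are taken and from whom, as well as on how common infection is. Scheduled screening of well people produces mostly negative samples. Testing people because they are ill produces few samples, with infections concentrated among them. Comparing the two with a 5% test answers a question whose result is largely set by the design.

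Section 1.7 presents these data as initial information on effectiveness. A significant four-group result could be read as a difference in infection or in detection between programmes when neither exists. This is separate from the fact that module and daycare centre cannot be told apart.

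**Working it through.** **Inputs from the protocol.** Minimum persons are 105, 105 and 185 in Modules 1, 2 and 3 (section 7.5). Samples per person over 12 weeks are 24, 12 and 24 (section 4.3.1). Module 4 has 275 children and workers, household size 3.5, and 279 expected recommended tests (section 7.5). Up to 28% of infections in children are asymptomatic (section 1.6), so at least 72% are symptomatic.

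**The plan's own figure.** The printed product 3.5 × 275 × 0.025 × 12 equals 288.75, not 279, a gap of 9.75 or 3.5%. I use the printed 279 and show the effect of 288.75.

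**Assumptions not in the protocol.** The 12-week attack rate *a* is the same in every module, and each infection gives one counted positive. In Module 4 only the symptomatic share *s* is tested. I take *s* from 30% to 72%, because the 28% figure concerns children and household members include adults. Crediting Modules 1–3 with every infection favours a small ratio.

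**Positivity at a = 2%**

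| | Module 1 | Module 2 | Module 3 | Module 4 |
|---|---|---|---|---|
| Tests | 105 × 24 = 2,520 | 105 × 12 = 1,260 | 185 × 24 = 4,440 | 279 |
| Positives | 105 × 0.02 = 2.1 | 2.1 | 185 × 0.02 = 3.7 | 962.5 × 0.02 × *s* = 5.78 to 13.86 |
| Positivity | 0.083% | 0.167% | 0.083% | 2.07% to 4.97% |

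Here 962.5 = 3.5 × 275. Module 4 supplies 279 of 8,499 tests (3.3%) but 5.78/13.68 = 42% to 13.86/21.76 = 64% of the positives.

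**Ratio of Module 4 to Module 1.** (*a* × 962.5 × *s* / 279) ÷ (*a* / 24) = 82.8 × *s*. The attack rate cancels. Participation in Modules 1–3 also cancels, since it scales positives and samples alike.
- *s* = 0.30 gives 24.8.
- *s* = 0.72 gives 59.6.
- With 288.75 tests the multiplier is 80, giving 24.0 and 57.6.

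**Simulation with equal infection rates.** This used each module's sampling days, an assumed 8-day detectable window, an assumed 14-day absence after a positive, and participation in Modules 1–3 of 37.5% or 100%. The four-group chi-squared test at 5% rejected in 81–99.6% of runs at a 1% attack rate, 95–100% at 2%, and over 99.9% at 5%. With so few positives the chi-squared approximation is rough, so these figures show what the named test would do if applied plainly.

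**Sampling frequency.** With one positive per infection, Module 2 positivity is 24/12 = 2 times that of Modules 1 and 3. The contrast is weak. At an assumed 0.2% per person-week, 105 × 12 × 0.002 = 2.52 positives in each of Modules 1 and 2. Comparing 2.52/2,520 with 2.52/1,260 gives chi-squared 0.63, p = 0.43. In the simulation Module 1 against Module 2 rejected in 3–20% of runs.

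If every repeat positive counts instead, expected positivity is the point prevalence at any frequency: 0.02 × 8/84 = 0.19%. The two-fold difference then disappears, and the fault becomes treating repeat samples from one person as independent. Against 0.19%, Module 4 is still 2.07/0.19 ≈ 11 to 4.97/0.19 ≈ 26 times higher.

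**The case against.** Several points on the other side stand.

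- **Consequence.** A reader might infer that this comparison would steer the choice of programme for the follow-on trial. Section 1.6 does not support that. Planning depends on meeting the acceptance criteria, and programmes are selected on acceptability and feasibility.
- **Frequency.** A reader might infer that twice-weekly sampling must halve positivity. That needs about one counted positive per infection. The protocol does not say that a person found positive leaves routine sampling. Section 4.3.1.8 leaves re-admittance to the health authorities, and section 4.3.3 stops sampling only for those seropositive at the start.
- **Module 4 measure.** It is tempting to say that Module 4 has no detection measure. Section 7.1 lists no positivity proportion for oropharyngeal swabs, but the Synopsis gives the number and cost of swabs, throat swabs included, per detected case, and the cost analyses in 7.1 are not limited by module.
- **Yield per test** is a real property of a programme and useful for costing. It is not an artefact in itself. Only its use in a between-module test is at fault.
- **P-values.** A very small p-value could be produced from expected counts, but those counts are fractional and the cells tiny, so it should not be quoted.
- **Detail.** How symptomatic home samples, case-module tests and repeats are handled may properly sit in an analysis plan.

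The strongest defence is that section 7.2 calls all analyses exploratory and promises cautious interpretation. Caution helps with chance and multiplicity. It does not help with a contrast whose direction the design fixes, and the choice to test all four groups is made in the protocol itself.

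**Conclusion.** The concern holds for the four-group and pairwise testing of PCR positivity, and symptom status is what drives it. With equal infection rates and one counted positive per infection, Module 4 positivity is about 25-fold (30% symptomatic) to 60-fold (72% symptomatic) that of Module 1. The attack rate does not affect these ratios. They do depend on the assumed symptomatic share, the section 7.5 test count and the one-positive assumption, and the gap stays at 11-fold or more when repeat positives count. For Module 4 the per-test unit is inferred from the endpoint's name, since section 7.1 spells it out only for swabs and saliva.

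The frequency effect is secondary and conditional. The endpoint is secondary and exploratory, so the matter is moderate. It is worth correcting because the test as written would almost always report a difference that says nothing about infection or detection.

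**What to change.** In section 7.2, delete PCR positivity from the endpoints tested across all four groups. Section 7.2 already limits costs, absent days and closures to descriptive methods, so this endpoint can be treated the same way.

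Report per-test positivity descriptively within each module, separating:
- routine samples from asymptomatic persons;
- symptom-triggered tests, including home samples from symptomatic children;
- case-module tests.

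In section 7.1, add persons with a detected infection, each counted once, per person-weeks. Report this descriptively, with Module 4 index persons and household members shown separately and not tested against Modules 1–3. Counting persons removes the frequency effect: at a 2% attack rate the simulation gives about 1.9% in each of Modules 1–3. It does not make Module 4 comparable, because that module would still find only symptomatic infections, 0.6% (30% symptomatic) to 1.4% (72%) of household members.

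The cost is wording in two sections and a reason-for-sample field, derived from the sampling documentation in section 6.1 and the symptom questionnaire. No new samples are needed. There would be no four-group p-value, and intervals will be wide because events are few.

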### **3 STUDY POPULATION**

#### **3.1 Selection of participating centers**

The study aims to include between 7 and 11 of the approximately 80 daycare centers located in the town of Würzburg for a study period of 12 weeks. For logistical reasons, larger daycare centers ( $\geq 50$  children) will be included preferentially. The selection of daycare centers will be carried out in cooperation with the office for youth, family and social affairs at Würzburg City Council using the following selection criteria:

...for the daycare centers in which modules 1 and 2 will be implemented:

- one daycare centre each, with a minimum of 100 children cared for at the centre and a minimum of 5 childcare workers
- consent of daycare centre's management to implementation of the study

...for the 1-3 daycare centers in which module 3 will be implemented:

- daycare centers with a minimum of 50 children of age  $\geq 2$  years cared for per centre (at least 175 children across all centers) and a minimum of 5 childcare workers per centre (at least 10 across all centers)
- consent of daycare centre's management to implementation of the study

... for the daycare centers in which module 4 will be implemented:

- between 4 and 6 daycare centers with a minimum of 250 children cared for and a minimum of 25 childcare workers across all centers
- consent of daycare centre's management to implementation of the study

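### Between-module significance tests treat individuals as independent although modules are delivered to whole, non-randomised centres (one each in Modules 1 and 2); the stated precision also ignores clustering

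*Protocol*

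**What the plan says.** **Allocation.** Section 3.1 selects centres with the city council and does not randomise them. For Modules 1 and 2 it asks for "one daycare centre each, with a minimum of 100 children cared for at the centre and a minimum of 5 childcare workers". Module 3 has its own criteria, "for the 1-3 daycare centers in which module 3 will be implemented". Module 4 has 4 to 6 centres (up to 5 in the Synopsis). No centre is planned to run two modules.

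**Tests.** Section 7.2 sets the level: "The significance level will be set to 5% for all analyses". For the primary measure it says: "The rate of acceptance will first be compared between all modules 1 to 3 using the chi-squared test". For drop out, initial consent, blood sampling, serology and PCR it plans four-group tests; the text reads "proportion of positive PCR tests will, in a first step, compare all four groups". It continues: "Subsequently, pairwise comparisons will be carried out using appropriate post-hoc tests". Baseline and week-12 psychosocial values are also compared between modules. No term for centre or family is named.

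**Intervals.** "The primary endpoints will be estimated as 95% confidence intervals using the Wilson score method". Section 7.5 derives half-widths from raw counts: 9.1, 8.7, 6.9 and 5.4 points for Modules 1 to 4.

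**ICC.** Where possible, "an ICC value (intraclass correlation) for the daycare centers will be calculated as a basis for sample size estimation" of the later cluster-randomised trial.

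**The concern.** The unit that receives a module is the centre, but the unit of the test is the person. Children in one centre share staff, management and local opinion, and siblings share the parents who decide on consent. With one centre per module, the chi-squared statistic compares two centres that also differ in protocol. It cannot attribute a difference to either, and it overstates the evidence that there is a protocol difference.

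Three further points follow from the same layout.

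- The primary intervals are too narrow if read as the acceptance of a protocol in general. Section 1.6 reads them in that direction when it expects similar drop out if a programme continues unmodified in the next study.
- An ICC taken across centres absorbs module differences unless module is in the model.
- The four-group comparison of PCR positivity sets screening of asymptomatic people (Modules 1-3) beside testing of symptomatic people (Module 4). Refusal of scheduled samples, one of the drop-out measures in Section 7.1, does not apply to Module 4, which schedules no respiratory samples.

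At stake are module differences reported as significant when they may be centre differences, overstated precision, and a weak ICC passed on to the next trial.

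**Working it through.** **Inputs.** From the protocol: n = 105, 105 and 185 persons in Modules 1-3 and 279 recommended tests in Module 4; rates 30%, 37.5%, 37.5% and 70%; level 5%; centres 1, 1, 1-3 and 4-6. Assumed, because the protocol gives none: centre ICC of 0.01, 0.02 or 0.05; a common true rate of 35% for the test simulation; three Module 3 centres and five Module 4 centres unless stated otherwise.

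**1. The plan's own precision.** Wilson half-width = z·√(p(1−p)/n + z²/4n²) / (1 + z²/n), with z = 1.96.

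| Module | n, p | Computed | Stated |
|---|---|---|---|
| 1 | 105, 30% | 8.6 | 9.1 |
| 2 | 105, 37.5% | 9.1 | 8.7 |
| 3 | 185, 37.5% | 6.9 | 6.9 |
| 4 | 279, 70% | 5.35 | 5.4 |

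The values for Modules 1 and 2 look interchanged. The Module 4 product 3.5 × 275 × 0.025 × 12 is 288.75, not 279. Both are side issues; 279 is kept below. The figures fit a design effect of 1, so no clustering was allowed for.

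**2. False rejection of the chi-squared test with no module effect.** Design effect for one centre of 105: D = 1 + 104 × ICC = 2.04, 3.08 and 6.20. For Module 1 v 2 the statistic is then roughly D times a chi-squared variable on 1 df, so the rejection rate is about P(χ²₁ > 3.84/D): 17%, 26% and 43%. Beta-binomial simulation agrees closely:

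| Assumed ICC | Module 1 v 2 | Modules 1-3, three Module 3 centres | Modules 1-3, one Module 3 centre |
|---|---|---|---|
| 0.01 | 17% | 21% | 27% |
| 0.02 | 27% | 35% | 43% |
| 0.05 | 44% | 60% | 68% |

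Between-centre degrees of freedom within module are 0 in Modules 1 and 2, 0-2 in Module 3 and 3-5 in Module 4. No cluster-adjusted test is therefore available for Module 1 v 2.

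**3. Half-widths with clustering by centre.** D = 1 + (m − 1) × ICC, then Wilson at n/D.

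- Module 3, m = 185/3 = 61.7. ICC 0.02: D = 2.21, effective n = 84, half-width 10.2. ICC 0.05: D = 4.03, effective n = 46, half-width 13.5. Stated: 6.9.
- Module 4, m = 279/5 = 55.8. ICC 0.02: D = 2.10, effective n = 133, half-width 7.7. ICC 0.05: D = 3.74, effective n = 75, half-width 10.2. Stated: 5.4.
- Module 1, if its interval is read as the rate over centres: the nominal 95% interval covers about 82%, 72% and 55% of the time at ICC 0.01, 0.02 and 0.05.

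Clustering by family or household would add to these.

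**4. The ICC.** Pooled over five centres of Modules 1-3 with no module term and a true ICC of 0, the estimate averages 0.006 at the protocol's rates (30/37.5/37.5%) and 0.14 at assumed rates of 20/40/60%. Within Module 3 it is essentially unbiased but imprecise. For an estimate of 0.05 with k = 3 and m = 62, F = (1 + 61 × 0.05)/(1 − 0.05) = 4.263. Dividing by the F(2, 183) quantiles 3.764 and 0.0253 gives 1.133 and 168.4. ICC = (F − 1)/(F + 61) then gives 0.002 to 0.73. This is a normal-theory interval, so only a guide for binary data.

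**The case against.** The strongest defence is that nothing decisive rests on these tests. Comparison of acceptance between modules is a secondary endpoint, and Section 7.2 calls every analysis exploratory and asks for cautious reading. A separate statistical analysis plan is foreseen and could deal with clustering. Much of this stands and limits the severity. It does not remove the point. The caution accompanies the decision not to adjust for multiplicity, and the use of separate centres is cited there as a reason not to adjust. For Modules 1 and 2 no later analysis method can supply the missing centres.

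Stronger readings that the protocol does not support:

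- *Programmes will be chosen on p-values.* Section 1.6 makes the next study depend on a programme exceeding its own success level, and selects on acceptability and feasibility. No between-module p-value enters.
- *Module and centre are fully confounded throughout.* This is exact for Modules 1 and 2, and for Module 3 with one centre. Otherwise centres are nested in Modules 3 and 4, and some between-centre variance can be estimated.
- *The acceptance test counts repeated swabs or household episodes as independent.* Acceptance is one yes/no value per person, and Module 4 is not in that test. Only shared centre and family matter.
- *Post-hoc tests are fixed for acceptance.* They are stated for the other endpoints; for acceptance the text names only the chi-squared test.
- *All the Wilson intervals are wrong.* For Modules 1 and 2 they are fair for those centres, siblings apart.
- *The ICC will be wrong.* It is planned only if possible, and nothing says it will be pooled without a module term.
- *No drop-out measure fits all four modules.* Parental withdrawal of consent exists in each of them, and Section 7.2 does not say which measure is tested.
- *Twice-weekly sampling halves PCR positivity per sample.* That needs exactly one positive sample per infection at either frequency, which is not stated.

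**Conclusion.** The concern holds in this limited form. The chi-squared comparison of acceptance cannot separate module from centre for Modules 1 and 2, or for Module 3 if one centre is used, and its nominal 5% level is not the real one. Even an assumed ICC of 0.01 raises false rejection to about 17% for Module 1 v 2 and 21% for Modules 1-3; at 0.05 it is 44% and 60%. The four-group tests of other endpoints share this weakness, and the PCR comparison also mixes different populations.

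The stated precision is optimistic wherever it is meant to speak for more than the centres observed: at assumed ICCs of 0.02 and 0.05, by a factor of roughly 1.5 to 2 in Module 3 (10.2/6.9 to 13.5/6.9) and 1.4 to 1.9 in Module 4 (7.7/5.4 to 10.2/5.4). Any centre ICC will be contaminated if pooled without a module term, and very imprecise if taken within Module 3.

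All clustering figures rest on assumed ICCs, equal centre sizes or nearly so, and clustering by centre alone. Severity is should-fix: the comparisons are secondary and exploratory, and the selection rule does not depend on them.

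**What to change.** In Sections 7.2 and 7.5, and the Synopsis to match:

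1. Remove the between-module significance and post-hoc tests. Report centre-level rates and module differences descriptively, labelled as module and centre combined.
2. Keep Wilson intervals for Modules 1 and 2, but label them centre-specific and allow for siblings.
3. Use cluster-adjusted intervals for Modules 3 and 4 (for example Wilson at the effective sample size, with centre and family or household as clusters). Restate the precision of both modules over a range of assumed ICCs.
4. Report PCR detection per person in Modules 1-3, and Module 4 separately. Limit any drop-out measure shown for all four modules to withdrawal of consent.
5. Estimate the ICC only within Modules 3 and 4, give its confidence interval, and size the next trial over a range of ICCs.

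The cost is wording, wider intervals and fewer p-values; no new data are needed. Little is lost by dropping the tests: even with independent individuals, 105 per module gives only about 21% power to distinguish the assumed 30% from 37.5%.
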